#### Secondary outcomes

Secondary outcomes include the change in general and specific quality of life questionnaires and in the patient’s perceived walking distance, speed, and ability to climb stairs.

#### Behavioral process variables

Process variables are those that can influence and explain initial and behavioral change over time. These psychological variables will play an important role in the change process as initial predictors in explaining the onset of behavioral change and as mediators and/or moderators in explaining the maintenance of change.

#### Additional variables

Sociodemographic, clinical, and physical data will be collected from the electronic medical record of the participants, through self-report and clinical interview. Data on physical capacity will be collected through two tests (treadmill test and 6-min test).

### Participant timeline {13}

Time 0 (t0) will be performed as a screening evaluation to ascertain inclusion criteria. Measurements will take place at time 1 (t1 - baseline assessment), 3 months after t1 (time 2: t2), and 6 months after t1 (time 3: t3). The schedule of enrolment, interventions, and assessments is shown in Fig. 1. Participants’ recruitment has already begun.

**Fig. 1 Fig1:**
[figure not shown]
Schedule of enrollment, interventions, and assessments

### Sample size {14}

The sample size was calculated for an effect size of 0.25, a statistical power of 80%, and a significance level of 5%; á priori 57 participants will be needed in each of the groups (G*Power software, version 3.1.9). This calculus was based on previous studies (*F* tests, ANOVA: repeated measures, within-between interaction) [15, 17]. The calculated sample size is expected to be reached by the end of May 2022.

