**Methods:**

This is a single-center, prospective, three-arm, single-blind, randomized, controlled, superior clinical trial with stratified and blocked random allocation. Three hundred participants with PAD and IC will be recruited from an Angiology and Vascular Surgery Department, Centro Hospitalar Universitário Porto (CHUPorto), Porto, Portugal. All patients will receive the same medical care recommended by  current guidelines. Participants in all three groups will receive a personalized prescription for an HBET program and a behavioral change and motivational intervention. Participants in experimental groups 1 and 2 will receive a smartphone with the WalkingPad app to monitor exercise sessions. Experimental group 2 WalkingPad app will have a built-in virtual assistant that will promote behavioral change and provide motivational support. Participants allocated to the active control group will not receive the m-health tool, but a practice diary to encourage monitoring. The  program will last for 6 months with three evaluation moments (baseline, 3, and 6 months). The primary outcome will be the change in distances walked (maximal and pain-free) from baseline to 3 and 6 months. Secondary outcomes will be changes in quality of life, patients’ perception of resistance, and walking speed.

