## Statistical methods

### Statistical methods for primary and secondary outcomes {20a}

The first step in the data analysis plan will be the screening of data to detect errors and missing values, although missing data is not expected in the questionnaires, as the data collection will be carried out in person with a researcher who will guarantee its complete completion. Missing values may be present when a participant withdraw or refuse to participate in the assessment, or missing values in physical tests due to physical limitations or difficulties in performing physical performance tests (e.g., treadmill test). Second, a summary of baseline sociodemographic, clinical, physical, and psychological variables will be provided through descriptive statistics. Third, comparisons will be made between the three groups to examine whether there are differences between the groups at baseline in all variables. As the sample was stratified, differences in fundamental variables such as age and maximal walking distance are not expected to be found. In addition, differences at baseline between participants who will complete the study and those who drop out will be examined. Fourth, primary outcome analyses will be conducted on an intention-to-treat basis, including all participants analyzed as randomized. The primary outcome will be analyzed using multiple regressions with adjustment for MWD, PFWD, and FWD. A mixed ANOVA will be performed to test the mean differences between the three groups (between-subject factor) and over the three measurement points (in-subject factor). Results will be reported as the difference in MWD, PFWD, and FWD from t1 to t2, t2 to t3, and t1 to t3, as well as the mean differences between GE1 and GE2, and ACG with 95% confidence intervals. To determine the minimal clinically important difference (MCID), a change in scores for the primary outcome will be calculated by subtracting the baseline outcome from the t2 (3 months) and t3 (6 months) outcomes for each participant. The least important difference (MID) for improvement and deterioration will be defined by the upper and lower limits of the 95% confidence interval of the mean change in MWD, PFWD, and FWD [71]. Twenty meters was defined as MCID [17]. However, a recent meta-analysis [19] showed significant heterogeneity in the magnitude of effect estimates for MWD (*χ*^2^ = 16.4, *p* = 0.022) and PFWD (*χ*^2^ = 19.6, *p* = 0.003). The mean change (SD) in MWD for patients randomly allocated to home exercise or programs with no exercise plan ranges from 24 (166) to 402 (391) m and PFWD changes range from 21 (81) to 182 (249) m.

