## Trial status

At the time of submission, this trial was already recruiting participants. This is version 2.0 of the protocol, last changes on March 9, 2022; expected date for completion of recruitment: April 30, 2022; expected date for the end of data collection: October 30, 2022; study end date: November 2022.

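### 57 per group does not follow from the printed G*Power inputs, the implied 171 is not reconciled with 300 or with the recruitment dates, and 80% power is not shown for the pairwise hypothesis

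*Protocol article*

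**What the plan says.** The Sample size section (item 14) gives the inputs: "The sample size was calculated for an effect size of 0.25, a statistical power of 80%, and a significance level of 5" per cent. The test is G*Power's F test "ANOVA: repeated measures, within-between interaction", and the result is that "57 participants will be needed in each of the groups". Three groups make 171. The section adds that "This calculus was based on previous studies" but gives no correlation among the repeated measures, no nonsphericity epsilon, no effect-size option and no dropout allowance.

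The Abstract (Methods) says "Three hundred participants with PAD and IC will be recruited", and the Recruitment section (item 15) repeats 300. The retention section (item 18b) cites dropout of 12 to 27.5% in earlier studies.

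On timing, the Sample size section says "The calculated sample size is expected to be reached by the end of May 2022". Trial status says "expected date for completion of recruitment: April 30, 2022; expected date for the end of data collection: October 30, 2022". The Participant timeline puts the last assessment 6 months after baseline.

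The Objectives state a pairwise hypothesis: ExpG2 (app with virtual assistant) does better than ExpG1 (app alone) and better than the active control. The Statistical methods section (item 20a) plans a mixed ANOVA of three groups by three time points and also between-group mean differences with 95% confidence intervals. It adds "Twenty meters was defined as MCID".

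**The concern.** A sample-size paragraph that names the software, test, effect size, power and alpha should lead back to its own answer. This one does not, and under the default option the gap is large. The reader cannot tell whether the trial was sized at 57, 171 or 300, or which number or date ends recruitment.

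There is also a question of what the 80% refers to. The test that was powered is a 4-degree-of-freedom interaction over all groups and times. The claim to be made is ExpG2 against each of two comparators. If the 80% is carried over to those comparisons, a null pairwise result may be read as adequately powered when the document has not shown that.

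**Working it through.** **Inputs.** From the Sample size section: f = 0.25 (read as Cohen's f, the scale for this test), power 0.80, alpha 0.05. From the Abstract and Statistical methods: k = 3 groups, m = 3 measurements. Not stated, so varied: correlation ρ and epsilon ε.

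**1. Attempt to reproduce 57 per group (171 in total).** Default option: noncentral F with λ = f²·N·m·ε/(1−ρ), df1 = (k−1)(m−1)ε, df2 = (N−k)(m−1)ε. Smallest total N in equal groups with at least 80% power:

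| ρ | ε | Total N | Power at that N | Power at 171 |
|---|---|---|---|---|
| 0.5 | 1 | 36 | 82.3% | over 99.9% |
| 0.3 | 1 | 48 | 81.0% | over 99.9% |
| 0 | 1 | 69 | 82.0% | 99.8% |
| 0 | 0.5 | 108 | 80.9% | 95.4% |

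Example, first row: λ = 0.0625 × 36 × 3/0.5 = 13.5, df 4 and 66.

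Alternative effect-size options, same degrees of freedom:
- λ = f²(N−k)(m−1)ε (SPSS type): 102 at ε = 1, 123 at 0.75, 162 at 0.5.
- λ = f²·N·(m−1)ε (Cohen type): 99 at ε = 1, 159 at 0.5.

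None of these is 171. The nearest, 162, would have 82.8% power at N = 171 (λ = 0.0625 × 168 × 2 × 0.5 = 10.5, df 2 and 168).

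**2. 57 as a total.** The default option returns 57 in total for some unstated pairs: ρ = 0.15 with ε = 1 (80.4%), ρ = 0.3 with ε = 0.75 (80.0%), ρ = 0.5 with ε = 0.5 (82.0%). At ρ = 0.5 and ε = 1, a total of 57 would have 96.8%.

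**3. 171 against 300.** Allowing for the cited dropout: 171/0.88 = 194.3, so 195; 171/0.725 = 235.9, so 236. Going from 300 to 171 would need a loss of 1 − 171/300 = 43%.

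**4. Dates.** 30 April plus 6 months is 30 October, so Trial status is consistent within itself. The Sample size section expects the calculated size a month later. A participant with baseline in May would have the 6-month assessment in November, after data collection ends.

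**5. Pairwise power at 57 per arm.** No pairwise effect is stated. If f = 0.25 means one group differing from two equal groups, then f = d√2/3, so d = 3 × 0.25/√2 = 0.53. Two-sided t-test, alpha 0.05:
- d = 0.53: 80.1%
- d = 0.50: 75.4%
- d = 0.53 after 12% dropout (57 × 0.88 ≈ 50 per arm): 74.7%
- d = 0.53 after 27.5% dropout (57 × 0.725 ≈ 41 per arm): 66%

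**6. In metres, for illustration.** Item 20a quotes SDs of change of 166 to 391 m for MWD and 81 to 249 m for PFWD. At 57 per arm, d = 0.53 is then 0.53 × 166 = 88 m to 0.53 × 391 = 207 m for MWD, and 0.53 × 81 = 43 m to 0.53 × 249 = 132 m for PFWD. A 20 m between-group difference would have about 6 to 10% power for MWD and 7 to 26% for PFWD.

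**The case against.** Several points on the other side have weight.

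- **57 per group can be reached.** The SPSS-type option with ε = 0.75 and 27.5% dropout gives 123/0.725 = 170; with ε = 0.5 and 5% dropout it gives 162/0.95 = 171. This stands as a warning against diagnosing the cause. It does not rescue the paragraph, because these routes need an epsilon, an effect-size option and a dropout allowance that it does not state. A condensed article may leave such settings to the full protocol, so their absence alone is not the point. The point is that the inputs printed do not lead to the result printed.
- **The powered test is a planned analysis.** The mixed ANOVA is in the Statistical methods. That is right, so powering the interaction is not an error. What remains is that its 80% does not transfer to the pairwise hypothesis.
- **300 may be the pool before screening.** The Recruitment section describes identification from a database, followed by invitation and eligibility assessment, and 57 is a minimum. So this is not a strict contradiction. But the Abstract speaks of participants to be recruited, and nothing links the two numbers.
- **Both dates are labelled expected.** True, but they still disagree by a month, and the 6-month assessment is part of the primary outcome.

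A reader might also infer that 57 per arm lacks pairwise power. The document does not support that as a flat statement: no pairwise effect is fixed, and d = 0.53, a natural reading of f = 0.25, reaches 80% unadjusted with no dropout. Nor does it support saying that 20 m is undetectable. The 20 m figure is introduced through each participant's change score, not as the between-group design target, the quoted SDs come from trials that the protocol itself calls heterogeneous, and no SD is given for the 6-minute walk test.

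**Conclusion.** The point holds in this form. The printed inputs give a total of 36 to 108 under the default option (ρ from 0 to 0.5, ε from 0.5 to 1) and 99 to 162 under the alternatives, not 171. If 171 are randomised, the omnibus power under the default option with ε = 1 is at least 99.8%, before any dropout. That 57 is a total read as a per-group number is plausible but unproven, since it needs unstated settings.

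The 171 and the 300 are unreconciled, with dropout explaining at most 236. The recruitment dates conflict by one month. Power for ExpG2 against each comparator is not shown; it may be about 80% or well below, depending on the effect assumed and on dropout.

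These results assume that 0.25 is Cohen's f, equal groups and three measurements. The pairwise figures use a t-test without multiplicity adjustment. Nothing here shows that the trial is too small or needs more patients.

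**What to change.** - Rerun and restate the calculation with ρ, ε and the effect-size option. Mark 57 as total or per group, and give the power that the chosen size actually delivers.
- Name one randomised target with its dropout allowance, and say what 300 denotes (screened, invited or randomised).
- Add the difference detectable with 80% power for ExpG2 against each comparator at that size, and do not present the 80% as power for the pairwise comparisons. If 20 m is mentioned, limit it to the treadmill figures at the quoted SDs.
- Reconcile the recruitment date in the Sample size section with Trial status, so that data collection ends no earlier than the last baseline visit plus 6 months.

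The cost is a short recalculation and protocol wording, with perhaps a month's shift in the end of data collection. The power statement may look less favourable for the pairwise claims. No extra patients are needed.

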### Recruitment {15}

Three hundred patients with PAD and IC, aged between 50 and 80 years, and with a MWD between 50 and 500 m, will be identified and recruited from the outpatient database of the Angiology & Vascular Surgery Department, Centro Hospitalar Universitário Porto (CHUPorto), Porto, Portugal, by a vascular surgeon member of the team. Eligibility for the study will be tested using clinical medical records and a screening evaluation. The listed participants will be contacted by phone and invited to participate in the study. The invitation will include a brief description of the study and the benefits of participating. For those who show interest in participating, a clinical, physical, and psychological screening assessment will be scheduled at the hospital—time 0 (t0 before allocation). In this assessment (t0), participants will sign a written consent and will be assessed (1 h ±) to determine particular and specific eligibility criteria. If there is an impediment to participation (e.g., COVID-19), the patient will be contacted later.

## Assignment of interventions: allocation

### Sequence generation {16a}

After the identification of patients through consultation of the outpatient database, the fulfillment of the inclusion criteria in the screening session and the patient’s agreement to participate in the study, a random sequence will be created using a random number allocation software, by a researcher external to the team involved in the execution of this study, in order to guarantee the concealment of the allocation of participants by the different groups. Randomization will be carried out in blocks with four strata and the eligible participants will be randomly assigned to three groups, in blocks of multiples of five, and will be stratified according to (i) age (50 to 65 years old; 66 to 80 years old) and (ii) MWD at the baseline (50 to 275 m; 276 to 500 m). The entire process will be overseen by a researcher who will not be directly involved in the intervention or assessments. This researcher will inform the research team of the final allocation of each participant.

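### Blocks in multiples of five split equally over three arms only at 15, 30 and so on, so the stated rule does not secure the equal groups the sample size assumes

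*Protocol article*

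**What the plan says.** Under Sequence generation {16a}, the protocol article states "Randomization will be carried out in blocks with four strata", the strata being two age bands crossed with two bands of baseline maximal walking distance (MWD). It continues that "the eligible participants will be randomly assigned to three groups, in blocks of multiples of five". It names no specific block size and no allocation ratio.

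Under Sample size {14}, "57 participants will be needed in each of the groups", which makes 171 in all and implies 1:1:1. Recruitment {15} gives a larger target: "Three hundred patients with PAD and IC, aged between 50 and 80 years". That would be 100 per arm if the arms are equal.

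Concealment mechanism {16b} describes the allocation a second time, as spreadsheet random numbers with sequential assignment to the three groups within the age and walking subgroups. It gives no block size either.

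**The concern.** Permuted blocks are used to hold the arms at the intended ratio throughout recruitment and within each stratum. They do this only if the block size is a multiple of the sum of the ratio terms, which is three for three equal arms. A rule stated as multiples of five meets that condition only at some sizes, and the two smallest sizes it permits (5 and 10) do not meet it.

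A reader therefore cannot tell whether the list is 1:1:1 and the sentence is loosely worded, or whether the list departs from 1:1:1. In the second case, what matters is whether the deficit moves between arms or always falls on one. A moving deficit costs little. A fixed one would change the allocation ratio and cost precision in every comparison with that arm.

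**Working it through.** **Inputs.** Three arms, four strata and block sizes in multiples of five (Sequence generation {16a}); 57 per group, so 3 × 57 = 171 (Sample size {14}); 300 to be recruited (Recruitment {15}). Two assumptions are mine: the four strata are equally frequent, and an indivisible block uses its most even split.

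The 57 is taken as stated, because only the equality of the groups matters here. The G*Power settings that were tried did not return 171. For example, the 3 × 3 within-between interaction at effect size 0.25, with correlation 0.5 and sphericity correction 1, needs 36 in total. The article gives neither of those last two values, so this is a separate question and nothing below depends on it.

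**Step 1: divisibility.**

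| Block size | Remainder on division by 3 | Most even split |
|---|---|---|
| 5 | 2 | 2:2:1 |
| 10 | 1 | 4:3:3 |
| 15 | 0 | 5:5:5 |
| 20 | 2 | 7:7:6 |
| 25 | 1 | 9:8:8 |
| 30 | 0 | 10:10:10 |

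The pattern repeats, so one multiple of five in three splits equally. The recruitment target of 300 is exactly 20 blocks of 15.

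**Step 2: the same arm is always short (blocks of 5).** The shares are 0.4, 0.4 and 0.2.

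- At 171: 68.4, 68.4 and 34.2, or about 68/68/34. At 300: 120/120/60.
- The variance of a two-arm contrast is proportional to 1/p₁ + 1/p₂, which is 3 + 3 = 6 under equal allocation.
- Contrast with the short arm: (1/0.4 + 1/0.2)/6 = 7.5/6 = 1.25, so 25% more variance. The standard error ratio is √1.25 = 1.118, about 12% more.
- Contrast between the two large arms: (1/0.4 + 1/0.4)/6 = 5/6 = 0.83, about 17% less variance.

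For blocks of 10 with the extra place always in the same arm, the shares are 0.4, 0.3 and 0.3, or about 68/51/51 of 171. The contrast between the two smaller arms has (1/0.3 + 1/0.3)/6 = 1.11 times the variance, and a contrast with the larger arm has (1/0.4 + 1/0.3)/6 = 0.97 times.

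**Step 3: the short arm is drawn at random in each block.** Stratified permuted blocks were simulated. The gap is the largest arm minus the smallest, over the whole trial.

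| Scheme | Mean gap, 171 (95th percentile) | Mean gap, 300 (95th percentile) |
|---|---|---|
| Blocks of 5, rotating | 6 (12) | 8 (15) |
| Blocks of 15 | 3 (6) | 3 (6) |
| Blocks of 6 | 2 (4) | 2 (4) |
| Blocks of 3, 6 and 9 in random order | 2 (4) | 2 (4) |
| Simple randomisation | 13 (25) | 17 (34) |

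A gap of 6 at 171 is about 60/57/54. The contrast between the two smaller arms then has (1/57 + 1/54)/(2/57) = (1 + 57/54)/2 = 1.03 times the variance, or 3% more.

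Within one stratum of 40 patients (eight blocks of 5), the mean gap is about 2.7. Simple randomisation gives 6.2. Blocks of 3, 6 and 9 in random order give 1.2, with a maximum of 3.

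**The case against.** The strongest reply is that the sentence can be satisfied without any imbalance. A block of 15 is a multiple of five, gives five patients per arm and fits 300 exactly, and the authors may have meant five per arm. An article may also leave exact block sizes to the full protocol. This stands as far as it goes: the rule is under-specified, not shown to be unworkable. It does not dispose of the point, because the article does publish a rule and most sizes that rule allows cannot deliver the equal groups planned elsewhere.

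The second reply is that the consequence is small. With a rotating short arm, blocks of 5 still balance arm sizes better than simple randomisation. The planned regression and mixed ANOVA accept unequal groups, and no bias follows. All of this stands. Even under a fixed 2:2:1 split, 300 recruits would leave 60 in the smallest arm, above 57 before dropout.

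A reader might go further and infer one of three things that the article does not support.

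- **That the trial has a 40/40/20 allocation.** This needs the same arm to be short in every block, which is stated nowhere.
- **That no multiple of five can work.** Blocks of 15, 30 and 45 do.
- **That the expected baseline comparability is undermined.** The statistical methods section says "As the sample was stratified, differences in fundamental variables such as age and maximal walking distance are not expected to be found". That expectation rests on stratification, not on equal arm sizes. An unequal ratio applied alike in every stratum would leave age and MWD comparable between arms.

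**Conclusion.** The point holds in limited form. As worded, the block rule does not ensure the 1:1:1 allocation implied by equal group sizes, and the article gives nothing from which the actual ratio could be reconstructed.

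The size depends on a fact the article does not give. If the list used blocks of 15 or 30, there is no loss beyond incomplete last blocks. If it used blocks of 5 with a randomly rotating short arm, the loss is a few patients and about 3% of variance. Only a fixed short arm would matter, at 25% more variance for contrasts with that arm. The simulated gaps assume equally frequent strata.

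Severity is minor to moderate: a specification error in a core design statement, with no demonstrated bias and probably little loss of precision.

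**What to change.** 1. In Sequence generation {16a}, replace the multiples-of-five rule with block sizes divisible by three within each of the four strata: for example 3, 6 and 9 in random order, or 15 if that was meant. Apply this to any remaining allocations.
2. State the 1:1:1 ratio explicitly.
3. Report the block sizes and the ratio used so far. If indivisible blocks were used, say how the short arm was chosen.

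The cost is a corrected sentence or two and, if patients remain to be allocated, regenerating the unused part of the list. The article expects recruitment to finish on 30 April 2022 (Trial status) and the calculated sample size to be reached by the end of May 2022 (Sample size {14}). Few allocations may therefore remain, and the third item is the one most likely to be useful.
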